# Effectiveness of two physical therapy interventions, relative to dental treatment in individuals with bruxism: study protocol of a randomized clinical trial

**DOI:** 10.1186/1745-6215-15-8

**Published:** 2014-01-07

**Keywords:** Bruxism, Physical therapy modalities, Massage, Muscle stretching exercises, Relaxation therapy, Imagination

## Abstract

**Background:**

Bruxism is a parafunctional habit characterized by grinding and/or clenching of the teeth. It may happen while awake (awake bruxism) or while sleeping (sleep bruxism). In adults, the prevalence is 20% for the awake bruxism and 8% for the sleep bruxism. Peripheral, central, and psychosocial factors influence the disorder, which may predispose to pain in the masticatory muscles and neck, headache, decreased pain thresholds in the masticatory and cervical muscles, limitation mandibular range of motion, sleep disorders, stress, anxiety, depression, and overall impairment of oral health. The aim of this study is to compare two distinct physical therapy interventions with dental treatment in pain, mandibular range of motion, sleep quality, anxiety, stress, depression, and oral health in individuals with bruxism.

**Methods/Design:**

Participants will be randomized into one of three groups: Group 1 (*n* = 24) intervention will consist of massage and stretching exercises; Group 2 (*n* = 24) will consist of relaxation and imagination therapies; and Group 3 (*n* = 24) will receive dental treatment. The evaluations will be performed at baseline, immediately after treatment, and at 2-month follow-up. Pain intensity will be assessed using the visual analogical scale, while pain thresholds will be determined using dolorimetry. Mandibular range of motion will be assessed using digital pachymeter. Sleep quality will be assessed by the Pittsburgh Sleep Quality Index, anxiety by the State*-*Trait Anxiety Inventory, stress by the Perceived Stress Scale-10, depression by the Beck Depression Inventory, and oral health will be assessed using the Oral Health Impact Profile - 14. Significance level will be determined at the 5% level.

**Discussion:**

This project describes the randomization method that will be used to compare two physical therapy interventions with dental treatment in the management of pain, mandibular range of motion, sleep quality, anxiety, stress, depression, and oral health in individuals with bruxism. The study will support the practice of evidence-based physical therapy for individuals with bruxism. Data will be published after study is completed.

**Trial registration:**

ClinicalTrials.gov, NCT01778881

## Background

The second edition of the International Classification of Sleep Disorders (ICSD-2) defines sleep bruxism as a stereotyped movement disorder characterized by grinding and/or clenching of teeth during sleep [1-5]. Awake bruxism is a semi-voluntary activity of teeth clenching that is rarely associated with audible sounds. The prevalence of awake bruxism is around 20%, while sleep bruxism affects around 8% of adults [4-6].

Peripheral, central, and psychosocial factors are relevant to the pathophysiology of bruxism [5,6], which may predispose to pain in the masticatory muscles and neck, headache, decreased pain thresholds in the masticatory and cervical muscles, limitation mandibular range of motion, sleep disorders, stress, anxiety, depression, and overall impairment of oral health. Bruxism is also associated with symptoms of other oral disorders [2,3,5].

Although some studies associate bruxism with craniofacial pain, the cause-effect relationship is not yet fully established [7-9]. Pain is not present in all individuals with bruxism, but studies show that repetitive activities related to parafunctional habits are considered important factors perpetuating pain [10]. Studies indicate that clenching and/or grinding of the teeth can trigger levels of muscle sensitization post exercise in the masticatory system, leading to damage of muscle fibers and surrounding tissues [8,11]. Currently the focus is on adaptation model of pain, which proposes that pain arises from muscle hyperactivity and, in turn, reduces muscle activity for the protection of the masticatory system [12].

Recent international consensus formed by a group of bruxism experts affirms the bruxism can be identified by anamnesis and physical examination, and confirmed with specific questionnaires [2,5], although there is also the polysomnography conducted in sleep laboratories [9,13].

Because bruxism is a multifactorial disorder, single specific treatments are not available, and multidisciplinary approaches administered by teams formed by dentists, physiotherapists, and other health professionals are often necessary [4-6]. Most treatment strategies are conservative, reversible, and symptomatic, aiming to prevent the consequences of the disorder [5,14,15].

Currently, physical therapy focuses mainly in two objectives: to decrease the adverse effects of bruxism to the masticatory system, and to increase self-awareness about this parafunctional habit. Techniques include therapeutic exercises, manual therapy, cognitive behavioral therapy, electrotherapy, acupuncture, postural awareness, and muscular awareness relaxation [15-23]. Dental treatments are often necessary, whose overall goal is to re-establish the occlusal harmony [4-6]. Among the several approaches, direct restoration of the dental surface using composite resin is a good option in order to re-establish incisal guides, promoting esthetic improvement and better function and occlusion [24,25].

In clinical practice, intra and extra oral massage of the masticatory muscles and massage of the cervical muscles are used and are associated with local circulation and metabolic improvements, as well as with decreasing muscle tonus [15]. Stretching exercises aim to increase mandibular range of motion, therefore decreasing pain and allowing for better mandibular rest positioning [16]. Relaxation therapies, such as progressive muscle relaxation, consist of a series of procedures involving implementation of controlled cycles of contraction and relaxation of different muscle groups. These techniques promote self-awareness of muscle tension and education on principles of muscle relaxation in activities that are relevant to normal life. Diaphragmatic breathing training and imagination (learning to create mental images of relaxed environments or activities) are relevant pieces of these therapies [18]. The literature is not clear regarding which physical therapy interventions are most effective for individuals with bruxism; therefore, more randomized controlled trials (RCTs) are necessary to clarify these questions. Moreover, little is known about the effect of two physical therapy interventions with dental treatment in individuals with bruxism.

Studies focusing physical therapy treatments to improve symptoms of bruxism such as massage of the masticatory and cervical muscles [15], stretching exercises [16], and relaxation therapies [18] are few and often do not describe in detail the treatment. Even rarer are studies that compare physical and dental therapies in individuals with bruxism [14,18]. Accordingly, our study adds to the evidence-based physical therapy practice addressing bruxism.

### Study aim

The aim of this study is to compare three treatments: two distinct physical therapy interventions (massage with stretching and relaxation and imagination therapies) with dental treatment in individuals with bruxism. In particular, we aimed to focus on pain, mandibular range of motion, sleep quality, levels of anxiety, stress, and depression, as well as on the overall status of oral health.

The hypothesis of this study is that the individuals with bruxism who receive one of physical therapy interventions (massage and stretching or relaxation and imagination therapies) will have greater reduction in pain intensity levels and better mandibular range of motion, sleep quality, levels of anxiety, stress and depression, and overall status of oral health compared to individuals who receive dental treatment as assessed immediately after the 6-week physical therapy intervention and that these benefits will be maintained until reassessment 2-month follow-up.

## Methods/Design

This study will be a RCT comparing two physical therapy interventions with dental treatment. Physical therapy will last 40 minutes and will happen twice a week for 6 weeks. Sessions will be conducted by the same physical therapist. Dental treatment will consist of two individual sessions conducted 1 week apart, each of it lasting 2 hours.

### Enrollment and eligibility criteria

The sample will consist of 72 patients, with established diagnosis of bruxism, that will be referred by Department of Dentistry at the School of Odontology, University of São Paulo.

#### Inclusion criteria

• Sleep Bruxism diagnosed according to the criteria of the International Classification for Sleep Disorders (ICSD) of the American Academy of Sleep Medicine (AASM) [1];

• Self-report of awake bruxism, documented by positive response to the question developed following the recommendations of Pintado [26];

• Aged between 18 to 60 years;

• A minimum pain intensity score of 3 on the Visual Analogical Scale [27].

#### Exclusion criteria

• More than two missing teeth, except third molars;

• Systemic and/or degenerative diseases;

• Arthrogenic or mixed temporomandibular disorder (TMD) according to the Research Diagnostic Criteria for Temporomandibular Disorders (RDC/TMD), axis I [28];

• Neurological or psychiatric diseases (with the exception of anxiety and depression);

• Using medications that influence sleep or motor behavior;

• Periodontal disorders;

• Abuse of alcohol and/or illicit drugs;

• Removable dentures, superior and/or inferior;

• Total dentures;

• Direct trauma or past surgery in the orofacial region;

• On physical, speech, dental, or psychological therapy at the time of study entry.

#### Procedures

All participants will be submitted to the same assessments, which will happen at baseline, immediately after treatment and at 2-month follow-up. Assessments will be conducted by a blinded researcher. Demographic and anthropometric data will be collected, as well as bruxism history. Examinations will also look for degree of severity of the temporomandibular disorder [29], bruxism [28,30,31], and pattern of cervical spine curvature [32]. Primary (pain and mandibular range of motion) and secondary (sleep, anxiety, stress, depression, and oral health) outcomes will be assessed.

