#### Mandibular range of motion

A digital pachymeter will be used in order to measure the mandibular range of motion (Digimess®) [36]. Reference points will be determined using the system proposed by Steenks and Wijer [37], using the maximal distance between the superior and inferior incisive teeth at the incisive line, with the participant seated, with aligned spine and feet touching the floor.

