### Group 3: dental treatment

Participants in this group will be treated by a dentist, and will be submitted to the same assessments and education. Restoring treatment will involve direct reconstruction of the anterior guides (incisive faces of the incisive and canine teeth) with resin. Two individual sessions will be conducted 1 week apart, and each will last up to 2 hours. Patients will be reassessed 30, 60, and 90 days after treatment end.

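### The unqualified claim of a blinded assessor cannot be relied on for mouth opening against the dental arm, because it is measured on the incisors that only Group 3 has rebuilt in resin

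*Protocol article*

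**What the plan says.** Procedures, on who assesses: "Assessments will be conducted by a blinded researcher". The same section applies one schedule to every arm: "All participants will be submitted to the same assessments, which will happen at baseline, immediately after treatment and at 2-month follow-up". It names the primary and secondary outcomes: "Primary (pain and mandibular range of motion) and secondary (sleep, anxiety, stress, depression, and oral health) outcomes will be assessed".

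Mandibular range of motion, on how this primary outcome is obtained with a digital caliper: "using the maximal distance between the superior and inferior incisive teeth at the incisive line".

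Group 3: dental treatment, on what is done to the teeth: "Restoring treatment will involve direct reconstruction of the anterior guides (incisive faces of the incisive and canine teeth) with resin". Tables 1 and 2, which describe Groups 1 and 2, contain no dental work.

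Background describes resin restoration of this kind as "promoting esthetic improvement and better function and occlusion", so a change in appearance is among its expected effects.

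**The concern.** The blinding statement covers all assessments, all visits and all comparisons. Yet one primary outcome makes the assessor look closely at the teeth that the Group 3 treatment alters and the other two treatments leave alone. An assessor who measured the same teeth at baseline has a direct cue to allocation from the first post-treatment visit onward.

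The cue identifies the comparator in the trial's hypothesis. Study aim predicts that the physical therapy arms will do better than dental treatment. An assessor who recognises Group 3 and shares that expectation could, without intending to, coax a little more or less opening from a patient. The same applies to dolorimetry, where the assessor applies the pressure by hand. These are the primary measures for which assessor blinding does real work. VAS pain is rated by patients, who can hardly be unaware of which treatment they had.

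**Working it through.** **Step 1. Which measurement and comparison are exposed?**

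| Measure | Produced by | Teeth must be seen? | Versus Group 3 | Group 1 versus Group 2 |
|---|---|---|---|---|
| VAS pain (primary) | Patient | No | Not affected by this cue | Not affected |
| Dolorimetry (primary) | Assessor, by hand, 4 muscles × 2 sides = 8 sites | No, pressure is on the skin | Exposed if the mouth is examined first, or at 2 months through memory | Not affected |
| Mouth opening (primary) | Assessor, caliper on the incisors | Yes | Exposed from the first post-treatment visit | Not affected |

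For mouth opening the exposure follows from three statements set side by side. The assessor is blinded (Procedures). The measurement is taken at the incisors (Mandibular range of motion). The incisors and canines are rebuilt in one arm only (Group 3: dental treatment). The remaining step, that the assessor notices the resin, is an inference. It is a strong one: the teeth are seen at close range before and after treatment, several front teeth are involved, and Background expects an aesthetic change.

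**Step 2. How much could it matter?** The plan gives no figure for assessor bias, so there is none to reproduce. The calculation below shows only how sensitive the planned test would be.

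Inputs:
- Group size from Sample size calculation: 24 with 20% attrition, so 24 × 0.80 = 19.2, taken as 19 per group.
- Test from Statistical analyses: analysis of variance with Tukey's post-hoc test, three groups, 5% level.
- Bias b, in SD units, shifting Group 3 relative to both other groups, with no true difference. **Assumed** values: 0, 0.25 and 0.5.

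Formulas:
- Error degrees of freedom = 3 × (19 − 1) = 54.
- The Tukey critical value is the 95% point of the studentized range for 3 groups and 54 df, q = 3.408. On the t scale it is 3.408 / √2 = 2.410.
- Non-centrality for one comparison with Group 3 = b × √(19/2) = 3.082 × b, which is 0, 0.771 and 1.541.
- The per-comparison rejection rate is the probability that |t|, non-central with 54 df, exceeds 2.410.
- The chance that at least one of the two comparisons with Group 3 rejects was obtained by simulation, because the comparisons share Group 3 and the pooled variance.

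| Assumed bias b (SD) | One comparison with Group 3 | At least one of the two |
|---|---|---|
| 0 | 1.9% | 3.6% |
| 0.25 | 5.7% | 9.9% |
| 0.5 | 20% | 31% |

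The bias adds one-for-one to the estimated difference between Group 3 and each of the other groups, whatever the true effect.

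**The case against.** **Recognition is not stated anywhere.** The resin may be tooth-coloured, and patients in Groups 1 and 2 may have old restorations: the exclusion criteria rule out dental therapy in progress at entry, not earlier work. This stands in part. The text supports likely recognition, not certain recognition. But a blinding claim should not depend on the examiner failing to notice rebuilt front teeth.

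**A reader might infer that assessment of the primary outcomes as a whole is unblinded.** The document does not support that. VAS pain, on which the trial is sized, is patient-rated, and nothing in this point helps the assessor tell Group 1 from Group 2.

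**A reader might also infer that blinding for dolorimetry is already lost.** That would assume the mouth is examined first. The article gives no order of assessments. Such detail can sit in a fuller protocol, so its absence is not itself an error, and the article happens to describe pain measures before mouth opening. What stands is narrower: the order matters, and even a good order does not help at 2 months if the same assessor saw the teeth at the first post-treatment visit.

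**The size is speculative.** This stands. A maximal distance read from a digital caliper is fairly objective, and no document supports a bias of 0.25 or 0.5 SD. Using an unadjusted two-sample t-test, one might quote a rise from 5% to about 12% or 32% for each comparison. The plan specifies Tukey's test, whose per-comparison rates are lower, as shown above.

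**Conclusion.** The concern holds in limited form. The protocol claims a property for all assessments that its own procedures undermine for one primary outcome, mouth opening, in the two comparisons with Group 3. The claim cannot be relied on there. It remains intact, as far as this point goes, for Group 1 versus Group 2. Dolorimetry versus Group 3 is at secondary risk, conditional on the order of measurement at the first post-treatment visit and on whether the same assessor returns at 2 months.

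The conclusion rests on one inference, that the restorations are usually recognisable at caliper distance. The illustrated error rates rest further on an assumed bias, 19 evaluable patients per group and equal variances. They show that a modest bias would matter and are not an estimate of what will occur. The point affects the credibility of part of the primary evidence and does not invalidate the trial.

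**What to change.** 1. **Order of assessment.** At every visit, record VAS, questionnaires and dolorimetry before any mouth-opening or intra-oral examination.
2. **Blinding statement in Procedures.** Do not claim assessor blinding for mouth opening versus Group 3. Do not claim it for 2-month dolorimetry versus Group 3 either, unless an existing team member who has not seen the teeth performs it. Keep the claim for Group 1 versus Group 2.
3. **Check on blinding.** Have the assessor record a guess of each patient's allocation after treatment, and report the results by group. This tests the inference on which the point rests.
4. **Reporting.** Present mouth-opening comparisons with Group 3 as not assessor-blind.

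The cost is a few sentences in the protocol and one extra item on the assessment form. No treatment, visit or sample size changes, and no extra staff are needed unless the team chooses to preserve dolorimetry blinding at 2 months by splitting the assessments. The price is an open statement that one primary outcome is not assessor-blind against the dental arm.

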### Randomization procedures

Participants will be randomized into one of three possible groups: Group 1 (*n* = 24) intervention will consist of massage and stretching exercises; Group 2 (*n* = 24) will consist of relaxation and imagination therapies; and Group 3 (*n* = 24) will receive dental treatment, through a computer-generated randomization schedule that will be performed by an independent researcher, not involved in other study procedures. The allocation of participants will be concealed by using consecutive numbered, sealed, and opaque envelopes. The flow of the study is summarized in Figure 1.

**Figure 1 F1:**
[figure not shown]
Flow diagram of the study.

## Outcome measures

### Primary outcomes

#### Pain

Pain intensity of the masseter, anterior temporalis, upper trapezius, and sternocleidomastoid muscles will be assessed using Visual Analogical Scales, constructed as a 10 cm ruler and clenching, muscular, and mental relaxation sensations and sleep difficulties will also be assessed using the same scale. On the left side of the scale, descriptors will be: no pain, no clenching, complete relaxation, and no difficulties falling sleep. On the right side, they will be: unbearable pain, maximum clenching, no relaxation, and being incapable of sleeping [27].

The pain threshold will be assessed using a dolorimeter with a rubber extremity with 1 cm of diameter. Perpendicular pressure on the skin will be applied on the trigger points of the upper trapezius, sternocleidomastoid, masseter, and anterior temporalis muscles, bilaterally. Participants will be seated straight, with feet touching the floor to the identification of the trigger points and demonstration of the dolorimeter technique in their forearm. After, patients will stay in dorsal decubitus with head discretely tilted to the opposite side of the assessments. Pain thresholds will be measured for each point, marked with a pencil. Lower thresholds are indicative of higher nociceptive sensation [33-35]. Pain thresholds will be considered positive when values are lower than 2.6 kg/cm^2^[33,36].

#### Mandibular range of motion

A digital pachymeter will be used in order to measure the mandibular range of motion (Digimess®) [36]. Reference points will be determined using the system proposed by Steenks and Wijer [37], using the maximal distance between the superior and inferior incisive teeth at the incisive line, with the participant seated, with aligned spine and feet touching the floor.

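### Mandibular range of motion, a primary outcome, is read between incisors whose incisal faces only the dental arm has rebuilt after baseline, so any added tooth length would read as lost opening in that arm

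*Protocol article*

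**What the plan says.** The Procedures section fixes the status of the outcome: "Primary (pain and mandibular range of motion) and secondary (sleep, anxiety, stress, depression, and oral health) outcomes will be assessed". The section on mandibular range of motion says that a digital caliper is used, "using the maximal distance between the superior and inferior incisive teeth at the incisive line". It also defers to a published scheme, "Reference points will be determined using the system proposed by" a cited source that the article does not reproduce. It mentions no vertical overlap (overbite) and no correction for restorations.

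The section on Group 3 describes the dental treatment: "Restoring treatment will involve direct reconstruction of the anterior guides (incisive faces of the incisive and canine teeth) with resin". The Background gives the purpose of such work: "direct restoration of the dental surface using composite resin is a good option in order to re-establish incisal guides".

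On timing, Procedures states: "All participants will be submitted to the same assessments, which will happen at baseline, immediately after treatment and at 2-month follow-up". In Group 3 the first reading therefore precedes the resin and the other two follow it.

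Study aim sets out what the hypothesis expects of physical therapy recipients against the dental arm: "better mandibular range of motion, sleep quality, levels of anxiety, stress and depression, and overall status of oral health compared to individuals who receive dental". Under Statistical analyses, the three groups are compared at each of the three time points by analysis of variance, with Tukey's test post hoc for parametric variables.

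**The concern.** The outcome is a distance between two tooth edges, taken as a measure of how far the jaw opens. In one arm, the treatment may move one or both of those edges between baseline and the later readings. A longer incisor leaves a smaller gap at the same jaw opening, so Group 3 could appear to lose motion that it has not lost. Groups 1 and 2 have no treatment that alters the teeth.

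The design features that usually protect a comparison do not help here. Randomisation and concealed allocation balance the arms at baseline, but the shift arises afterwards. A blinded assessor does not remove it, because it is physical and not a matter of judgement. A larger sample only makes a false difference easier to declare. The shift also runs in the hypothesised direction, so a favourable result on this outcome could not be attributed to jaw motion with confidence.

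**Working it through.** **The plan's own figures.** The plan gives no figure on this point. Its sample size (24 per group, 20% attrition) was set on pain VAS, and nothing below depends on whether that calculation is right. It supplies only the number of completers: 24 × 0.8 = 19.2, taken as 19 per arm.

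**Geometry.** Let T be the inter-incisal distance that would be read with unrestored teeth, and h the total length that resin adds to the two reference incisors along the caliper line.

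- Groups 1 and 2, all visits: reading = T.
- Group 3, baseline: reading = T.
- Group 3, after treatment and at 2 months: reading = T − h.

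If true opening is the same in all arms, the expected difference between physical therapy and dental treatment is 0 at baseline and h at both later visits.

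**Assumptions.** The article gives neither h nor the SD of opening. I take h = 1, 2 or 3 mm and SD = 5 or 8 mm. The shift in SD units is h/SD, from 1/8 = 0.125 to 3/5 = 0.60.

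**Test.** Three arms of 19 give 3 × 19 − 3 = 54 degrees of freedom. The Tukey critical value on the t scale is 2.41. The standard error of a difference between two arms is SD × √(2/19), which is 1.62 mm at SD 5 and 2.60 mm at SD 8. Example: h = 2 and SD = 5 gives an expected t of about 2/1.62 = 1.23.

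**Chance of a false significant result when true opening is equal in all arms** (pooled-variance test; first result column simulated, second from the noncentral t distribution):

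| SD (mm) | h (mm) | h/SD | Either physical therapy arm vs dental | One given arm vs dental |
|---|---|---|---|---|
| any | 0 | 0 | 3.6% | 1.9% |
| 5 | 1 | 0.20 | 7.6% | 4.3% |
| 5 | 2 | 0.40 | 20.9% | 12.8% |
| 5 | 3 | 0.60 | 43.4% | 29.6% |
| 8 | 1 | 0.125 | 5.1% | 2.8% |
| 8 | 2 | 0.25 | 9.9% | 5.7% |
| 8 | 3 | 0.375 | 18.6% | 11.3% |

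**What would cancel the shift.** Two corrected readings are possible.

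- Distance plus vertical overlap. If resin adds h to the overlap while the closed-jaw position stays the same, then (T − h) + (overlap + h) = T + overlap, and the shift disappears. If the resin changes the closed-jaw position, the overlap does not grow by the full h and cancellation is incomplete.
- Distance plus the two crown heights. (T − h) + (upper height + lower height + h) = T + upper height + lower height. This does not depend on the closed-jaw position and is in effect the distance between the gingival margins.

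**The case against.** The strongest objection is the cited reference-point system. If it adds vertical overlap to the inter-incisal distance, the shift largely cancels as shown above. We cannot see that source, so the possibility stands. It does not dispose of the point, because the sentence that defines the reading states only the inter-incisal distance.

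Second, the text does not say that the reference incisors are lengthened in every Group 3 patient. It names incisal faces of incisors and canines, but not the arch, the teeth treated in each patient or the length added. Resin on canines, or on surfaces that do not lengthen a reference incisor, would not shorten the reading. This stands, and it is why the claim is conditional. A reader might infer that Group 3 is bound to show reduced opening; the article does not support that.

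Third, the size rests on assumptions. At 1 mm and SD 8 the false-positive rate barely moves (5.1% against 3.6%), and the top figure pairs the largest shift with the smallest SD. Pain, the outcome behind the sample size, is not touched by this artefact. All of that is correct.

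Fourth, a reader might infer that no adjustment could remove the bias. That goes too far: a larger sample cannot, but recorded overlap or crown heights can.

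Finally, a reader might infer a blinding failure from "Assessments will be conducted by a blinded researcher", since the assessor measures at the restored teeth, and might propose taking this reading last at each visit. That ordering would not protect the 2-month visit if the same assessor had already seen the restorations, and the VAS is the patient's own rating. I make no claim that reading order preserves blinding.

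**Conclusion.** The point holds in conditional form. As printed, the protocol article defines a primary outcome by a landmark that one arm's treatment may move after baseline, and states no correction. The direction is known: against dental treatment and towards the hypothesis. The size is not. Under the assumed 1 to 3 mm and SD of 5 to 8 mm, with 19 per arm, the chance of a false finding against dental treatment by either physical therapy arm runs from about 5% to 43%, compared with 3.6% with no shift. For one given arm it runs from about 3% to 30%, compared with 1.9%. These figures rest on the assumed h and SD, on resin lying along the caliper line in the average Group 3 patient, and on no overlap correction being hidden in the cited system. The lower end is negligible and the upper end would make the range-of-motion result uninterpretable. Nothing in the article says which end applies, so the measurement should be fixed instead of relying on a small shift.

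**What to change.** At every visit and in all three arms, use one of the following and name it as the analysed range of motion:

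1. the distance at maximal opening between landmarks the resin does not touch, for example the gingival margins of the same upper and lower incisors; or
2. the inter-incisal distance plus the caliper-measured crown heights of the two reference incisors.

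If the cited system already adds vertical overlap, the protocol should say so, and should say how a change in closed-jaw position would be handled. The treatment itself need not change.

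The routine cost is revised assessment wording and about a minute per visit with the same caliper and assessor. The corrected reading is slightly noisier and less directly comparable with published incisal-edge values, so the uncorrected distance can be reported alongside it.

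There is a further cost because the Trials status section says recruitment is under way. For Group 3 patients already restored, the crown height before restoration can no longer be measured directly. Report a sensitivity analysis that leaves them out, or one that uses an estimated added length. The number affected grows until the change is made, so it should be made before further Group 3 patients are treated.
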